## Abstract

**Background::**

Motor deficits are common after stroke and are a major contributor to stroke-related disability and the potential for long-lasting neurobiological consequences of stroke remains unresolved. There are only a few treatments available for the improvement of motor function in stroke patients. However, the mechanisms underlying stroke recovery remain poorly understood, and effective neurorehabilitation interventions remain insufficiently proven for widespread implementation.

**Methods::**

Herein, we propose to enhance the effects of brain plasticity using a powerful noninvasive technique for brain modulation consisting of navigated transcranial magnetic stimulation (TMS) priming with transcranial direct current stimulation (tDCS) in combination with motor-training-like constraint-induced movement therapy (CIMT). Our hypothesis is that navigated low-frequency rTMS stimulus priming with precise location provided by neuronavigation on the healthy side of the brain and with anodal tDCS on the affected side combined with CIMT will induce a greater motor function improvement than that obtained with sham tDCS combined with CIMT alone. We predict that the application of this technique will result in a large reduction in cortical excitability and dis-inhibition in the affected hemisphere and lead to improvements in behavioral measures of hand function in stroke patients.

**Discussion::**

The proposed study, therefore, is important for several reasons. The results could potentially lead to improved stroke therapeutics, and the approach makes use of 2 potential pathways to modulate brain function.

**Trial registration::**

This study protocol was registered in Clinical Trials Registry (https://clinicaltrials.gov/ct2/show/NCT04646577).

**Ethics and dissemination::**

The study has been reviewed and approved by the Human Research Ethics Committee of the King Fahad Specialist Hospital Dammam. The results will be actively disseminated through peer-reviewed journals, conference presentations, social media, broadcast media, print media, the internet and various community/stakeholder engagement activities.

## Introduction

1

### Rising incidence and burden of stroke

1.1

Stroke is a primary cause of death and disability globally. It is caused by an interrupted blood flow due to thrombosis or embolism to the brain which results in loss of vision, sudden paralysis, and impaired speech. In less than 15% cases, stroke leads to hemorrhage or cardiac arrest. According to the Global Burden of Diseases, Injuries, and Risk Factors Study (GBD), stroke was responsible for 5.5 million deaths after ischemic heart disease globally (1). In United States, stroke occurs once every 40 s and someone dies every 4 minutes, with death rate estimated to 41.6% in 2007.^[1]^ The absolute numbers of stroke-affected people may increase due to aging population. It is not only the high mortality; 50% survivors suffer from chronic disability. Thus, stroke has serious economic and public health significance. It is estimated that stroke cost 73.7 billion dollars in 2010 in United States and is projected to be 1.52 trillion dollars in 2050 (in 2005 dollars).^[1]^ Weakness, caused by damage of cortical networks for movement and their projections and disuse-related mechanisms, is considered a major cause of disability.^[2]^ Impaired function is experienced in the upper limb of two third of stroke survivors.^[3]^ High blood pressure, the major risk factor for stroke, is very common in Kingdom of Saudi Arabia (KSA). Incidence of stroke in Saudi population is 29.9 per 100,000.^[4]^ It is the third leading cause of death and in many surviving patients; it is the devastating endpoint of cerebrovascular disease.^[2]^ The impact of acquired brain injuries, for example stroke, upon individuals, families, and society continues to increase due to both the aging of the general population and the increasing length of post-insult survival. Stroke-related neurologic deficits, including motor function deficits, are often persistent, exerting a negative effect on the patient's quality of life.

### Understanding stroke recovery mechanism based on brain plasticity is critical for developing new therapeutic approach

1.2

Brain plasticity is the ability of the brain to adapt to experiences, environmental pressure, and challenges which include brain damage.^[5,6]^ It happens within many levels, from molecules to cortical reorganization. There are multiple factors that influence the outcome of stroke, including the time after stroke, the lesion's location and the integrity of cortico-spinal tracts, and the cortical and subcortical connections. In general, each hemisphere undergoes neuroplasticity changes by means of regeneration, for example, axonal and dendritic sprouting with or without reorganization of cortical motor areas, for example, modulation of the synaptic plasticity or remapping of the functional representations by diminution of GABAergic inhibition, and increased NMDA receptor binding from lessoned areas onto the unaffected ipsilesional areas which surround the lesion or the homologous areas which are within the contralesional unaffected hemisphere.^[7,8]^

The latest literature specifies that noninvasive brain stimulation (NIBS) techniques (i.e. repetitive transcranial magnetic stimulation (rTMS) and transcranial direct current stimulation (tDCS)) can enhance the recovery of motor functions in chronic stroke patients. Two potential roles have been described for rTMS and transcranial direct current stimulation (tDCS) in stroke recovery:

(1)to inhibit, that is, downregulate, the healthy hemisphere, or(2)to enhance excitability of the lesioned hemisphere.

Downregulation of the contralesional hemisphere can lead to improved motor performance in the affected limb, thought to be through a reduction in interhemispheric inhibition to the lesioned side. Most of the spontaneous stroke recovery after the acute phase entails plastic changes within the brain.^[9]^ For rehabilitation, new measures should be adopted to facilitate plasticity of brain which help in changes to occur more rapidly and more completely. Since plasticity in the hemisphere with stroke lesions leads to good recovery, one therapeutic approach such as brain stimulation should be focused to enhance brain plasticity in these areas.

### Measurement of the cortical physiology and corticospinal tract integrity are important in terms of planning an effective treatment.

1.3

The progress in technologies which enable non-invasive exploration of the human brain have expanded our understanding of the reorganization of the brain after ischemic stroke.^[7–10]^ This kind of therapeutic approach solely relies on the functional and physiological status of each hemisphere and its balance between 2 hemispheres, which imply the importance of this physiological measure on planning an effective treatment strategy.

Cortical physiology could be measured by TMS using paired-pulse paradigm.

(1)short interval intracortical inhibition (SICI) is accepted to be GABAA-dependent since GABAA agonists increase SICI.(2)long interval intracortical inhibition (LICI) is moderated by a long lasting GABAB-dependent IPSPs and the enabling of pre-synaptic GABAB receptors on inhibitory interneurons.(3)Intracortical facilitation results from the net facilitation of mechanisms which are inhibitory and excitatory mediated by GABAA and NMDA receptors, respectively.(4)Glutamatergic cortical interneurons could be involved in intra-cortical facilitation given that it is reduced by NMDA antagonists, for example, dextromethorphan. Those measurements will enable us to shed light on how the new therapeutic approach had effect in terms of inhibition and excitation balance in each and between hemisphere.

Diffusion tensor imaging tractography (DTI) is a new technique which enables non-invasive visualization of the human brain's fiber tracts in vivo^[10–13]^ which mostly has an impact on future design and choice of rehabilitation methods for each individual patient.

Measurement of the corticospinal tract volume, fractional anisotropy, mean diffusivity, axial diffusivity and radial diffusivity will give us insight about inter-individual variability of the efficacy of the therapeutic intervention.

Constraint-induced movement therapy (CIMT) is an intervention which has been used, for the most part, for treating upper extremities of stroke patients, which is based on perilesional reorganization.^[14,16]^ many of those successfully treated so far have been chronic patients that experienced stroke at least 1 year before starting CIMT therapy. It is approximated that patients whom are responsive to substantial improvement resulting from CIMT represent at least 50% of the stroke population in total^[17]^ current data advocate that CIMT therapy enhances motor function within a 2week period.

The effects of the treatment remain stable for many months after the end of therapy, and everyday lives of patients are adjusted accordingly with treatment effects.

Recently in neuroscience, NIBS techniques like (TMS or tDCS) have shown the potential to investigate causal brain-behavior relationships and for the rehabilitation of many diseases. It is important to mention that advances in neuroscience mostly depend on the union of evidence from multiple methods. Given that every technique has limitations of its own, combining various approaches will be, theoretically, a clear advantage.

### Development of novel therapeutic approach combining motor learning and neuromodulation, which shared similar mechanism

1.4

As we know coupling cortical stimulation with motor learning might enhance motor recovery: As aforementioned, both strategies for enhancing motor recovery – motor learning and cortical stimulation - are associated with similar mechanisms of action – that is, increasing local excitability within the lesioned motor cortical area (possibly through synaptic strengthening) and decreasing it in the healthy contralateral hemisphere. Therefore we hypothesized that combining both therapies will enhance its individual effect on motor recovery. Indeed a few animal and human studies support such hypothesis. First, in an elegant study, Plautz et al noted that monkeys which were submitted to electrical stimulation which was subthreshold in combination with rehabilitative training multiple months after spontaneous recovery had improvements which were significant following therapy in motor performance, which persisted for several months.^[18]^ Also cortical mapping showed a large-scale surfacing of new hand representations within peri-infarct motor cortex, mainly within cortical tissue underlying the stimulating electrode.^[19]^ Second, a recent study showed that intensive rehabilitation therapy in combination with invasive epidural electrode has a significant improvement in motor function as compared with rehabilitation alone.^[20]^ Third, a recent study combining brain stimulation (rTMS) and motor learning (complex sequential finger motor task) showed that active motor cortex stimulation and motor training resulted in a significantly larger increase in motor cortex excitability in the affected hemisphere and enhanced motor performance accuracy as compared with motor training and sham stimulation.^[20]^ Therefore evidence supports that brain stimulation enhances the behavioral and neurophysiological effects of motor training in motor recovery.

There is sufficient evidence that NIBS induce neuroplastic changes which are mirrored in behavioral changes that can be observed. Albeit, the precise mechanism of NIBS in producing this neuromodulation in not well understood. Therefore, recent efforts to merge NIBS with neuroimaging in experimental paradigms were made to give a more methodical characterization of neuroplastic modulation by NIBS by way of using brain network analysis techniques.

### Genetic influence on inter-individual variability, plasticity and behavior

1.5

Genetic polymorphism is also a contributing factor to affect the brain's response to disease and injury. Brain-derived neurotrophic factor (BDNF) is involved in the modulation of synaptic plasticity which is activity-dependent in the human motor cortex. A common single nucleotide polymorphism (BDNF val66met) in BDNF gene, has been associated with a decrease in the secretion of BDNF which then decreases the activity-related cortical plasticity following healthy individuals’ motor training and is associated with more errors and deficient retention in short-term motor learning.^[21,22]^

We therefore hypothesize that neuronavigation 1 Hz rTMS on health side, which provides real-time feedback and allows stimulation only when trajectory, coil position and coil rotation are within consistent, pre-determined boundaries, will be a more potent effect on the excitability of specific local cortical networks (identified during the optimal site assessment), prime with tDCS on affected side will enhance the effects of CIMT on motor function recovery in chronic stroke patients. Until recently the use of noninvasive brain stimulation coupled with motor learning was limited as rTMS or tDCS alone.

Currently, detailed information about stroke or brain plasticity is not available in the Middle East.

## Methods

2

### Overall strategy

2.1

Overall Approach, Participants, and Feasibility: We propose to study 40 patients (above 18 years) with first-time clinical ischemic or hemorrhagic cerebrovascular accident. Individuals with preexisting neurological or psychiatric conditions, those with unstable medical conditions, and those on any medication that might alter the TMS-tDCS measures will be excluded. A written consent will be obtained, and all the subjects will have full neurological and medical examination. Furthermore, detailed neuropsychological and behavioral assessment will also be performed in different domains. All participants will undergo a neurophysiologic study of local cortical reactivity, plasticity, and network dynamics using TMS-EMG following stroke. Participants will be randomized to active treatment with 1 Hz rTMS prime with real anodal or sham tDCS by means of randomization stratification. This approach guarantee that both groups have a close distribution in regards to the degree of paresis. Participants will be gathered into groups (strata) defined by the degree of paresis (low and high functional) and then randomized separately within each stratum according to a block randomization of 4 to receive real 1 Hz rTMS prime tDCS/CIMT and sham tDCS/CIMT. All participants will undergo brain magnetic resonance imaging (MRIs) for morphometric analysis and diffusion tensor imaging, and serial neurological and neuropsychological exams.

We have developed a safe and reliable method combining TMS with EMG to characterize cortical reactivity, plasticity, and brain network dynamics in humans.^[23–27]^

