### Assessments – instruments of evaluation

2.3

A rater blinded to the treatment will assess the effects of the interventions using the instruments described below. Subject enrollment, consent checklist, and screening logs will be used as well as an inclusion and exclusion checklist to assist in prescreening measures. To assess treatment efficacy (motor function changes), we will use the following instruments:

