These instruments will be performed at the following time points by trained staff blinded to group assignment: during the week before the beginning of treatment (2) During day 5 and day 10 of treatment and (3) at 2 weeks of follow up, 4 weeks and 6 months after the end of treatment (Table 1). Moreover, to make sure that blinding is not broken within the duration of the study, we will use a questionnaire to assess the validation of the blinding at the end of the study. This questionnaire will ask both the participants and the rater whether the treatment was sham or active tDCS. The confidence of the responses will be rated accordingly, from 0 to 5, where 5 is total confidence and 0 is no confidence,

**Table 1 T1:** Stroke and plasticity schedule of events.

	Screening visit	Training and tDCS Visits (10 d)			Follow-up visit
	1	2	6	10	4 wk
Consent	X				
Inclusion/Exclusion	X				
Pregnancy Test if indicated	X				
PMH/Physical	X				
Demographics	X				
Taylor Hand Function Test	X				X
Purdue Pegboard Test	X				X
Fugl-Meyer Assessment of Motor Recovery	X				X
Modified Barthel Index	X				X
Modified Ashworth Scale	X				X
Visual analog scale	X				X
Mini Mental State Examination		X	X	X	X
TMS and tDCS Screen	X	X	X	X	X
Training		X	X	X	X
MRI	X		X		
Pre/Post TMS Side Effect Questionnaire		X	X	X	X

MRI = magnetic resonance imaging, tDCS = transcranial direct current stimulation, TMS = transcranial magnetic stimulation.

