### Constraint induced movement therapy (CIMT)

2.5

Each subject will receive 14 days (2-week period: 10 weekdays) of CIMT (using the same methodology as described in a recent multi-site clinical trial.^[15]^ furthermore, during the 10 weekdays of the treatment period, the individuals participating will come into the laboratory to train the affected arm for up to 6 hours a day, using a variety of tasks according to a behavioral technique termed “shaping.”

**Statistical power and data analysis Sample size** will be determined with reference to other studies that used similar endpoints. We assume that a standardized difference of 0.8 (the difference between groups divided by the standard deviation) is conservative to detect a clinically meaningful difference between groups (active 1 Hz rTMS prime with tDCS/CIMT and sham tDCS/CIMT). We will assume a type I error of 5% (alpha), a type 2 error of 10% (beta), therefore, the power is going to be 90%. A t-test will be used (Using the sample size calculation for a normal distributed population); where 15 individuals per arm will be needed (therefore, a total of 30). We expect a 20% rate of loss to follow up or drop out. Moreover, we will assume that individuals who drop out will not improve from the last measured point; therefore, the sample size will increase by 20% to 36 participants (18 per arm). Furthermore, in case of unexpected factors such as higher placebo response, we increased the sample size further to 40 patients.

**PROTECTION OF HUMAN SUBJECTS** This study aims to enroll adult patients with a history of cerebral infarct that is chronic and associated with stable and significant motor deficits. Both ischemic and hemorrhagic stroke subtypes will be included. The entry criteria for patient enrollment are the following:

(1)age 18 to 90;(2)first-time clinical ischemic or hemorrhagic cerebrovascular accident as noted in the radiological (or physician's) report;(3)the ability to extend =20° at the wrist and 10° at the metacarpophalangeal and interphalangeal joints of all digits;(4)participants must demonstrate adequate balance while wearing the restraint;(5)the ability to stand from a sitting position and the ability to stand for at least 2 minutes with or without upper extremity support;(6)weakness, defined as score of 15 to 55 (out of 66) on arm motor Fugl-Meyer scale; and(7)stroke onset more then 6 months prior to study enrollment.

*Exclusion criteria*:

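### A single published block size of 4 in each stratum makes about one third of allocations certain to anyone who can learn the earlier ones; randomly varying block sizes remove most of that certainty at almost no cost

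*Protocol article*

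**What the plan says.** Under Overall strategy, the protocol article forms two strata, "defined by the degree of paresis (low and high functional", and patients are then "randomized separately within each stratum according to a block randomization of 4". No other block size is mentioned. The sample size paragraph, printed under Constraint induced movement therapy (CIMT), implies equal arms ("the sample size will increase by 20% to 36 participants (18 per arm") and a final total of 40 ("we increased the sample size further to 40 patients").

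On blinding, the section on assessment instruments says "A rater blinded to the treatment will assess the effects of the interventions" and that the instruments are applied "by trained staff blinded to group assignment". An end-of-study questionnaire asks participants and the rater to guess the treatment, which implies that participants are meant to be blinded too. The article does not say whether the stimulation operator or the CIMT therapists are blinded.

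The arms are worded in two ways within Overall strategy. One is "Participants will be randomized to active treatment with 1 Hz rTMS prime with real anodal or sham tDCS", which can be read as rTMS in both arms. The other is "to receive real 1 Hz rTMS prime tDCS/CIMT and sham tDCS/CIMT", which reads as no rTMS in the control arm. The Methods part of the abstract and the sample size paragraph follow the second wording. The TMS methodology section describes a sham for tDCS and none for rTMS.

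**The concern.** In a block of 4 with two places per arm, the last allocation is fixed by the first three, and the third is fixed whenever the first two match. An observer who knows the block size, the stratum and its earlier allocations therefore knows some allocations in advance. The article itself supplies the block size.

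The rest could come from the treatment room. If control patients receive no rTMS and no sham rTMS, whoever runs the 30-minute rTMS session sees the arm. If that person also recruits, or talks to those who do, knowledge of the next allocation could influence who is enrolled and when. Entry requires stroke onset more than 6 months earlier, so enrolment is not urgent and could be delayed. A blinded rater does not protect against selection at entry, and with about 20 patients per arm a few steered patients could shift the comparison.

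**Working it through.** The article gives no predictability figure, so there is none to reproduce.

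**Inputs**
- Block size 4, two strata (Overall strategy).
- 1:1 allocation, from 18 per arm out of 36; total 40 (sample size paragraph).
- Assumption for every result below: the observer knows the stratum and all earlier allocations in it.

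**Step 1: certain allocations in one block of 4.** There are 4!/(2!·2!) = 6 equally likely orders. Positions 1 and 2 are never certain. Position 3 is certain if the first two match, which happens in 2 of 6 orders (1/3). Position 4 is always certain. Expected number per block: 0 + 0 + 1/3 + 1 = 1.333, and 1.333/4 = 33.3%.

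**Step 2: best-guess rate.** Guess the arm with more places left, and toss a coin if tied.
- Position 1: 0.5
- Position 2: 2/3
- Position 3: 1/3 × 1 + 2/3 × 0.5 = 2/3
- Position 4: 1
- Mean: (0.5 + 0.667 + 0.667 + 1)/4 = 70.8%, against 50% with no information.

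**Step 3: the whole trial, allowing for incomplete last blocks.**

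| Split of 40 over the two strata | Complete blocks | Certain allocations |
|---|---|---|
| Both sizes multiples of 4 (e.g. 20 + 20) | 10 | 10 × 1.333 = 13.3 (33.3%) |
| Both leave 2 over (e.g. 18 + 22) | 9 | 9 × 1.333 = 12.0 (30.0%) |
| One leaves 1, the other 3 (e.g. 17 + 23) | 9 | 12.0 + 1/3 = 12.3 (30.8%) |

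**Step 4: effect of varying the block size.** Simulated with 20 patients per stratum and each size equally likely, for an observer who knows which sizes are possible and all past allocations.

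| Block sizes | Certain allocations | Best guess right |
|---|---|---|
| 4 only | 33% (13.3 of 40) | 71% |
| 4 and 6 | about 6% (2.4 of 40) | about 69% |
| 2, 4 and 6 | about 4% (1.6 of 40) | about 70% |

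Varying the sizes removes most of the certainty but little of the guessing advantage.

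**Step 5: cost in balance.** The largest possible difference between arms within a stratum is half the largest block: 4/2 = 2 now, and 6/2 = 3 with blocks up to 6.

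**The case against.** A reader might infer that treating staff know the arm, so that one third of allocations simply are predictable. The article does not support this. It nowhere says that treating staff are unblinded; that follows only from silence on operator blinding, the absence of a described sham rTMS, and the arm wording without rTMS in controls. On the other wording both arms receive rTMS and differ only in tDCS, for which a sham with the same electrode position is described.

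Even an operator who knows the arm does no harm unless that knowledge reaches whoever decides on enrolment. The article does not say who enrols patients or how the list is held, and an article may leave this to the full protocol. If recruiters do not know past allocations, no allocation is certain.

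Two further strong readings fail. The boundary between the low and high functional strata has no stated cut-off, but an article may also leave that out, so it is no fault here. Nor would any resulting bias be wholly beyond repair: adjustment for the baseline scores would address imbalance in measured severity, though not in unmeasured factors.

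These objections make the point conditional and modest; stratified blocks of 4 are common and legitimate. They do not remove it. The single size is a rule that the article states and makes public, not a detail it leaves open, and a better rule costs almost nothing.

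**Conclusion.** The point holds as a conditional, low-cost improvement and not as a demonstrated bias. If those who enrol patients can learn earlier allocations in a stratum, 12 to 13 of 40 allocations (30% to 33%) become certain and a best guess succeeds 71% of the time. The figures assume 1:1 allocation and that the stated 4 is the number of patients per block. Whether the condition is met cannot be settled from the article. It is more plausible if controls receive no rTMS, and less so if both arms do. The direction and size of any bias in the treatment effect cannot be derived from the article.

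**What to change.** For patients not yet randomized:

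1. Generate the list with randomly varying block sizes within each stratum, for example a mix of 4 and 6, or of 2, 4 and 6.
2. Withhold the sizes from recruiting and treating staff.
3. Record the patient's stratum before the allocation is released.
4. State who is blinded, including the stimulation operator and therapists, and how past and future allocations are kept from recruiters. Since varying the sizes barely lowers the best-guess rate, this is the main safeguard.
5. Reconcile the two descriptions of the arms, because they determine what an operator can see.

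The cost is regenerating the list for the remaining patients and a few sentences of text. The downside is a possible within-stratum difference between arms of 3 instead of 2.
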